## Analysis and Reporting of Results

We will conduct an interim analysis when we have recruited 50% of the total sample size (230 women).

The initial analysis will examine the baseline characteristics of all randomised women, as an indication of comparable treatment groups, and include maternal age, race, height, weight, smoking history, past obstetric history (including previous perinatal loss), and chorionicity of the pregnancy. Any important differences in these prognostic variables will be controlled for in subsequent analyses. Outcome comparisons for women and infants will be analysed for the primary and secondary outcomes on an "intention to treat" basis, according to treatment allocation at randomisation. Continuous outcomes will be analysed using linear mixed model regression. Binary outcomes will be analysed using a generalised linear mixed model with a log link function and binomial distribution. A random effect to account for clustering of babies from multiple births will be included. If models do not converge, then alternative methods of accounting for multiple births using robust variance estimation will be explored. Results will be presented as relative risks with 95% confidence intervals. The level of significance will be 0.05 and all p values will be two-sided.

Pre-specified subgroup analyses will be by chorionicity of the pregnancy (monochorionic or dichorionic); collaborating centre; and actual mode of birth.

Approval to conduct this study has been obtained from the following research and ethics committees: Women's and Children's Hospital (Adelaide, South Australia); Lyell McEwin Health Service (Adelaide, South Australia); The Royal Women's Hospital (Melbourne, Victoria); Sydney West Area Health Service (New South Wales); Northern Sydney Central Coast (New South Wales); Mater Health Services (Brisbane, Queensland); Redcliffe-Caboolture Health Service (Queensland); Logan Hospital (Queensland); Townsville Health Service (Queensland); Mackay Base Hospital (Queensland); and Auckland City Hospital (New Zealand).

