### Trial Entry

At the first antenatal clinic or upon diagnosis, all women with a twin pregnancy will be given the trial information sheet, counselled by a member of the research team and encouraged to discuss the study with her family. A member of the research team will then obtain provisional, written, informed consent. To maximise the likelihood that women will receive the care allocated at randomisation, eligible women will be randomised from 36^6 ^weeks gestation. Eligibility and consent will be reconfirmed just prior to randomisation.

After the woman is eligible to be randomised, entry details will be recorded on the trial entry form, and the central telephone randomisation service at the Australian Research Centre for Health of Women and Babies, Discipline of Obstetrics and Gynaecology, University of Adelaide will be contacted. During a short telephone call, information to check eligibility will be sought that, describes the woman, enables stratification at randomisation so that similar women are allocated to the treatment arms, assists in follow-up and assists in the analysis of results. If an eligible woman does not agree to randomisation, minimal details will be recorded to complete the requirements for reporting of clinical trials (CONSORT).

Once all entry details are given at telephone randomisation and eligibility confirmed, a study number will be allocated to the woman by the central randomisation office, and the group to which the woman is allocated (either elective birth or standard care) will be stated. An investigator not involved with the treatment allocation of the women, using balanced variable blocks, will prepare the randomisation schedule. Stratification will be by collaborating centre and planned mode of birth (planned caesarean section or planned vaginal birth).

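### The primary adjustment set is chosen from observed baseline imbalance with no threshold, and the stated model includes neither stratification factor

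*Protocol article*

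**What the plan says.** All but one of the relevant statements are in the protocol article under Analysis and Reporting of Results.

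- **Baseline variables.** The characteristics to be compared "include maternal age, race, height, weight, smoking history, past obstetric history (including previous perinatal loss), and chorionicity of the pregnancy".
- **Covariate rule.** "Any important differences in these prognostic variables will be controlled for in subsequent analyses". The sentence that follows turns to the comparisons for the primary and secondary outcomes, so the rule covers the primary endpoint.
- **Model.** "Binary outcomes will be analysed using a generalised linear mixed model with a log link function and binomial distribution". For twins: "A random effect to account for clustering of babies from multiple births will be included".
- **Fallback.** "If models do not converge, then alternative methods of accounting for multiple births using robust variance estimation will be explored".
- **Effect measure.** "Results will be presented as relative risks with 95% confidence intervals".

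The randomisation is described under Trial Entry: "Stratification will be by collaborating centre and planned mode of birth (planned caesarean section or planned vaginal birth". In the analysis section, centre returns only as a subgroup. Mode of birth also returns only as a subgroup, and there it is the actual mode, which is observed after randomisation, not the planned mode used for stratification.

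**The concern.** In a randomised trial, baseline differences between arms arise by chance. How large a difference happens to be says little about whether adjusting for that variable helps; what matters is how strongly it predicts the outcome. A rule triggered by imbalance therefore uses the wrong criterion and makes the primary model depend on the data. With no definition of *important*, two competent analysts given the same baseline table could fit different primary models and report different relative risks.

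Factors used to stratify randomisation are normally carried into the primary model, because stratification removes between-stratum variation from the treatment comparison. An analysis that ignores the strata does not credit that removal and overstates the standard error when the factors are prognostic. Here the imbalance rule cannot bring them in either, because it reaches only the listed variables and neither factor is on the list.

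The third and smallest gap is the fallback. Non-convergence is foreseen, but the replacement is only to be explored, so the specific model would be chosen with outcome data in hand.

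**Working it through.** The plan gives no figure on this point to reproduce. Its 460 women, 16.3% and 6.7% (Sample Size) serve as inputs only.

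**1. How often chance alone could change the covariate set.** Seven items are listed: age, race, height, weight, smoking, past obstetric history and chorionicity. Assume that each is judged at p<0.05 and that they are independent. Then

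P(at least one flagged) = 1 − 0.95^7 = 1 − 0.698 = 0.302, about 30%.

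If correlation reduced the seven to five effective tests, the figure would be 1 − 0.95^5 = 23%; with three, 14%. The protocol states no p-value rule, so these figures are illustrative.

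**2. Consequences for error rates and intervals.** An illustrative null simulation assumed:

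- 460 women with two infants each, and an event rate of 16.3% in both arms;
- permuted blocks within 11 centres by planned mode (the article lists 11 ethics approvals);
- seven independent prognostic covariates and a shared mother effect;
- a log-link Poisson fit with variance clustered on the mother;
- 2,000 runs per scenario, with stratum effects set to none, moderate (planned-mode log-odds 0.8, centre SD 0.6) or strong (1.5 and 0.8).

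All effect sizes are assumptions. The Monte Carlo standard error of a 5% rate is √(0.05 × 0.95 / 2000) = 0.005.

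| Stratum effects | Unadjusted: type I error | Unadjusted: mean reported SE of log RR | Unadjusted: true SE | Adjusted for centre and planned mode: type I error | Adjusted: mean reported SE |
|---|---|---|---|---|---|
| None | 0.048 | 0.165 | 0.166 | 0.050 | 0.164 |
| Moderate | 0.045 | 0.168 | 0.164 | 0.055 | 0.162 |
| Strong | 0.038 | 0.171 | 0.162 | 0.050 | 0.158 |

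Omitting the factors overstates the SE by 0.1681/0.1644 − 1 = 2% (moderate) and 0.1713/0.1618 − 1 = 6% (strong). Adjustment lowers the reported SE by 1 − 0.1615/0.1681 = 4% and 1 − 0.1579/0.1713 = 8%. The true SE barely moves (0.1644 to 0.1640; 0.1618 to 0.1609), because stratified randomisation already balances these factors. What is lost is mainly precision in the reported interval.

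In the same runs, a mechanical rule that adjusts for any covariate differing at 5% gave a type I error of 0.034 to 0.043, so no inflation. Free choice of the most favourable of nine adjustment sets (none, each covariate singly, all seven) gave 0.057 to 0.086.

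**3. Log link with a normal random intercept.** This model does not bound a mother's risk below 1. For marginal risk p and twin ICC r (assumed), the intercept variance is s² = ln(1 + r(1 − p)/p), its mean is b = ln p − s²/2, and P(risk > 1) = 1 − Φ(−b/s).

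- Standard care, p = 0.163, r = 0.5: s² = 1.27, b = −2.45, P = 1.5%.
- Elective arm, p = 0.067, same s² = 1.27 (the plan describes one random effect): b = −3.34, P = 0.15%.
- For r from 0.1 to 0.7 the standard-care figure runs from 0.08% to 1.8%.

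A tail of this size makes fitting trouble foreseeable. It does not show that the fit will fail.

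**The case against.** The strongest objection is that this is a condensed article and the full analysis plan is not shown. The article never says that centre and planned mode will be left out, and an exact adjustment set is commonly deferred to that plan. This stands in part: one can say only that the described model and baseline list lack the factors, not that the final analysis will. It does not protect the imbalance rule. That rule is stated outright, and a later plan that fixed the covariates would have to override it. That the two factors predict the composite is also an assumption, not something the protocol documents.

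A reader might go further and infer three things that the document does not support.

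- *The error bars ignore the design.* They do not: the model has a random effect for twin pairs and the fallback also accounts for them. Only stratification is missing, and its omission errs towards conservative intervals.
- *The data pick the estimation method.* One model is named, there is one trigger for leaving it, the class of fallback (robust variance) is stated, and the relative risk is kept. The gap is that no specific fallback model is named.
- *The 5% level is inflated.* A mechanical imbalance rule did not inflate it. Inflation required choosing the model by its result, whereas the protocol makes baseline imbalance the trigger. The missing threshold leaves room for such a choice but does not prescribe it.

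**Conclusion.** The point holds in limited form. The primary adjustment set is not fixed in advance, because it depends on observed imbalance under an undefined criterion. The 30% figure indicates how often the set might change; it rests on a p<0.05 rule and independence, neither of which the protocol states, and it is not an error rate. The described analysis also leaves out both stratification factors. If they are prognostic, the reported standard error is too large by about 2% to 6% in the simulated scenarios, with a type I error as low as 0.038. The 0.045 and 0.048 results lie within simulation noise of 5%, so the effect is clear only when the factors are strong. The unnamed fallback is a minor gap in wording. None of this suggests intervals that are too narrow. The case for change is that the primary estimate should be reproducible from the plan and that the correction costs almost nothing.

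**What to change.** 1. Delete the imbalance rule. Keep the baseline table as description only.
2. Adjust the primary analysis in every case for planned mode of birth and centre, with a pooling rule for small centres set before outcome data are seen. Add any prognostic covariates only if named in advance; chorionicity is a natural candidate.
3. Report the unadjusted relative risk as a sensitivity analysis.
4. Keep non-convergence as the trigger, but name a single fallback, for example a log-link Poisson GEE with robust variance clustered on the mother, using the same covariates.

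The cost is a change of analysis wording, with no effect on recruitment or data collection. The small downside is that low-recruiting centres must be pooled for the model to fit. If a separate analysis plan already fixes these items, the protocol wording should be brought into line with it.

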### Sample Size

The incidence of serious adverse infant outcome is the principal endpoint of the trial. Using a composite neonatal morbidity and mortality index based on perinatal mortality, admission to NICU for greater than or equal to four days, and birthweight less than the third centile for gestational age at birth and infant sex, the occurrence of serious adverse neonatal outcome for infants of a twin pregnancy born at 37 weeks gestation or more is estimated at 16.3% [4]. To reduce this to the rate of 6.7% seen in singleton infants at the same gestational age [4], and adjusting for the clustering of twin infants within mothers, a sample size of 460 women with a twin pregnancy at ≥ 37 weeks gestation will be required, using a p-value of 0.05 (two tailed) and power 80%.

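### The log-link mixed model chosen first for infant binary outcomes need not return the ratio of arm risks if twins are moderately correlated; the marginal model now held as a fallback should be primary

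*Protocol article*

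**What the plan says.** Analysis and Reporting of Results (protocol article) fixes one first-choice model for every binary outcome, the primary composite included: "Binary outcomes will be analysed using a generalised linear mixed model with a log link function and binomial distribution". It continues: "A random effect to account for clustering of babies from multiple births will be included". On reporting: "Results will be presented as relative risks with 95% confidence intervals". Methods based on robust variance are to be explored only if this model fails to converge.

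Sample Size frames the effect as a contrast of risks per infant: 16.3% for twins, and "To reduce this to the rate of 6.7% seen in singleton infants at the same gestational age". The trial size of 460 women is described as "adjusting for the clustering of twin infants within mothers", but no within-pair correlation is given. The article does not state the distribution of the random effect, the fitting method, or how the relative risk is taken from the model.

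**The concern.** With a log link, the coefficient within mothers and the ratio of arm risks are the same number only while every mother's modelled risk stays below 1. A normal random effect has no upper limit. With a standard-care risk of 16.3%, a random effect wide enough to produce moderate twin correlation pushes some mothers past 1. The software must then do something about risks above 1, and what it does changes the coefficient.

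At stake are the headline relative risk and its interval, not the p-value. The Primary Study Endpoint section says an important benefit is needed to justify the policy, so the size of the effect matters. A coefficient that differs from the ratio of the arm risks printed beside it would be hard to explain. The fallback offers no protection where the model converges, because only non-convergence triggers it.

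**Working it through.** **Inputs.** From Sample Size: risks 16.3% and 6.7%, so RR = 0.067 / 0.163 = 0.411; 460 women. Assumed: 1:1 allocation (230 women per arm), a normal random effect, the same ICC in both arms, and the exponentiated coefficient reported as the RR. The ICC is not given, so a range is shown.

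**Can the ICC be read from the sample size?** For two-sided 0.05 and 80% power, infants per arm without clustering are [1.96·√(2·0.115·0.885) + 0.842·√(0.163·0.837 + 0.067·0.933)]² / 0.096² = 172.2, rounded up to 173. With pairs the design effect is 1 + ICC, and total women = 173·(1 + ICC), which is 173 to 346. The stated 460 is not reached at any ICC. It equals the 90% figure at ICC 1 (230·2). So the stated size does not reveal a planning ICC.

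**Why the two ratios part.** The model is log risk = b0 + b1·arm + u, with u normal, mean 0, SD s.

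- No cap: arm risk = exp(b + s²/2), where b = b0 or b0 + b1, so the ratio of modelled arm risks is exp(b1).
- Risk capped at 1: arm risk = exp(b + s²/2)·Φ(−b/s − s) + Φ(b/s), and the ratio is no longer exp(b1).

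Worked case, capped maximum likelihood in large samples, beta-binomial pairs, ICC 0.3. The fit gives b0 = −2.546, s = 1.312, exp(b1) = 0.375.

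- Share of standard-care mothers with uncapped risk above 1: 1 − Φ(2.546/1.312) = 1 − Φ(1.94) = 2.6%.
- Standard-care risk: 0.1854·0.735 + 0.026 = 16.2%.
- Elective-birth risk (b = −3.527): 0.0695·0.916 + 0.0036 = 6.7%.
- Averaged ratio: 0.414, against a coefficient of 0.375.

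So this fit describes the arm risks well; its coefficient is not their ratio.

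**Large-sample coefficients by fitting approach (true RR 0.411).**

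| ICC | Capped ML | Capped fit, averaged over mothers | Uncapped | Pseudo-likelihood |
|---|---|---|---|---|
| 0.1 | 0.412 | 0.413 | 0.413 | 0.395 |
| 0.2 | 0.402 | 0.415 | 0.421 | 0.393 |
| 0.3 | 0.375 | 0.414 | 0.435 | 0.413 |
| 0.5 | 0.283 | 0.407 | 0.501 | 0.443 |
| 0.6 | 0.220 | 0.406 | 0.576 | 0.444 |

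Relative to 0.411, the capped coefficient is 2% low at ICC 0.2 (0.402/0.411 = 0.98), 9% low at 0.3 and 31% low at 0.5. The uncapped one is 6% high at 0.3 and 22% high at 0.5. A variant that truncates the random effect so that no risk reaches 1 departs sooner: 0.339 at ICC 0.2 and 0.202 at 0.3.

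The uncapped fit errs for a different reason. It forces P(both affected)/p² = exp(s²) to be equal in both arms. At ICC 0.5 the data have 1 + 0.5·0.837/0.163 = 3.57 under standard care and 1 + 0.5·0.933/0.067 = 7.96 under elective birth. The compromise moves the fitted risks to 14.8% and 7.4%.

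The capped result is not only misfit to beta-binomial pairs. If the capped model is exactly true, exp(b1) is still 0.385 at a standard-arm ICC of 0.3 and 0.308 at 0.5.

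**Simulated trials, 230 women per arm.** Coverage of the true RR by the 95% interval:

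- Capped fit: about 95% at ICC 0.2, 90% to 94% at 0.3, and 73% to 85% at 0.5, depending on implementation; 91% to 98% of fits were usable at ICC 0.3 to 0.6.
- Uncapped fit: 92.3% at ICC 0.3 and 80.3% at 0.5.
- Marginal log RR with variance clustered on the mother: median 0.40 to 0.41 and coverage 95% to 96% at ICC 0.1 to 0.6.

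**No true effect.** Both arms share one distribution, so b1 = 0 however the model is fitted. At RR 1 and ICC 0.4 the capped fit gave a median of 1.00 and 95.7% coverage.

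**The case against.** The article states no normal random effect, no fitting method and no rule that the exponentiated coefficient is the reported RR. Such details commonly sit in an analysis plan, and their absence is no fault. That stands, and the point does not rest on it. What the article does fix is the order: mixed model first, marginal approach only after failure.

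The size of the problem depends on an ICC that the documents do not give. At 0.1 there is no practical bias. That also stands. Moderate correlation cannot be excluded, since the composite includes birth weight at or below the 3rd centile and NICU stays of four days or more, and twins share a mother and a gestation at birth. But no figure in the protocol supports 0.5 or 0.6.

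Some fits would not converge, and the fallback would then apply. A Laplace-approximated likelihood without a cap kept rising as the random-effect SD went from 0.3 to 2.2 at ICC 0.1, 0.2, 0.3 and 0.5, with no interior maximum. This limits the point for such software, but it leaves the choice of primary estimate to the software.

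A reader might infer that the planned analysis will exaggerate the effect of birth at 37 weeks. The documents do not support that: capped fits overstate, uncapped fits understate, and pseudo-likelihood falls on both sides. A reader might also infer that the primary test is invalid. It is not biased under no effect.

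**Conclusion.** The point holds as a conditional one. With a normal random effect, an ICC of about 0.3 or more and the exponentiated coefficient reported, the first-choice model can give a relative risk that differs from the design contrast of 0.41. Depending on an unstated fitting choice, the approaches tabulated above range from about 0.375 to 0.44 at ICC 0.3 and from about 0.28 to 0.50 at ICC 0.5. At ICC 0.2 or less the capped and uncapped fits are within about 2% of the truth. The exact loss of coverage depends too much on implementation to state as one figure. This is a cheap improvement to a stated method; it does not show that the trial's result would be wrong.

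**What to change.** In Analysis and Reporting of Results, reverse the order. For infant binary outcomes, name as primary a marginal log-link model: generalised estimating equations, log-binomial or Poisson, with robust variance clustered on the mother. Report the two arm risks beside each relative risk.

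If the mixed model is kept, use it as a sensitivity analysis, or report its averaged (standardised) risk ratio in place of the exponentiated coefficient. Averaging repairs a fit that caps risks at 1; it does not help an uncapped fit, where the averaged ratio equals the coefficient.

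The cost is one sentence, with no extra women or data and standard software. The small downside is that robust variance rests on a large-sample approximation, which is weaker for rare secondary outcomes.

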### Benefits of induction of labour

Elective induction of labour has been proposed in a number of clinical situations, with the aim of reducing adverse outcomes for both women and their infants. Induction of labour after 41 weeks gestation in women with a singleton pregnancy has been shown to be associated with a reduction in perinatal mortality [11]. Retrospective studies indicate that the risk of stillbirth and early neonatal death in a twin gestation correlates with that seen beyond 41 weeks in a singleton gestation [2,3,5-7]. The question to then be considered relates to prospectively defining the "post-term" twin pregnancy, and to assess the role of induction of labour for women with a post-term twin pregnancy in reducing perinatal mortality. The potential advantages of elective timing of birth in women with a twin pregnancy at 37 weeks' gestation of a reduction in perinatal mortality and morbidity have to be balanced against any associated increase in the risk of caesarean section and potential risks for the infants associated with early birth, including respiratory distress syndrome and need for admission to the neonatal unit.

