### Elective Birth Group

Women allocated to the elective birth group will be planned for elective birth from 37 weeks gestation. Where there is a plan for vaginal birth, this will involve induction of labour. Where there is a plan for caesarean birth, this will involve an elective caesarean section. The planned mode of birth will be assessed and determined by the woman and the obstetrician caring for her.

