### Standard Care Group

For women allocated to the standard care group, birth will be planned for 38 weeks gestation or later, according to the hospital where they expect to give birth. Where there is a plan for vaginal birth, this will involve either awaiting the spontaneous onset of labour, or induction of labour if required. Where there is a plan for caesarean birth, this will involve an elective caesarean section (where possible booked after 38 weeks and as close to 39 weeks gestation as possible). The planned mode of birth will be assessed and determined by the woman and the obstetrician caring for her.

If earlier birth (before 38 weeks gestation) is considered appropriate due to the development of complications, this will be carried out either by induction of labour or by caesarean section, as determined by the woman and the obstetrician caring for her. However, the woman will remain in the standard care group for the purposes of analysis.

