### Secondary Study Endpoints

*1. ***Antenatal medical and obstetric complications**including: pre-eclampsia or eclampsia *(systolic blood pressure ≥ 140 mmHg and diastolic ≥ 90 mmHg on two occasions four hours apart or more, and one of proteinuria (≥ 300 mg/24 hours or spot urine creatinine ratio ≥ 30 mg/mmol), renal insufficiency (serum plasma creatinine ≥ 0.09 mmol/L or oliguria), liver disease (elevated serum transaminases &/or right upper quadrant pain), neurological disturbances (convulsions, hyperreflexia with clonus, severe headache with hyperreflexia, persistent visual disturbances), or haematological disturbances (thrombocytopaenia, disseminated intravascular coagulopathy, haemolysis),)*[16] antepartum haemorrhage requiring hospitalisation; and abnormal umbilical artery Doppler study *(absent or reversed end diastolic flow as detected by ultrasound examination).*

2. **Labour and birth complications**including: induction of labour for medical or obstetric complications; meconium stained liquor; cardiotocogram (CTG) abnormality during labour (*fetal tachycardia (fetal heart rate greater than 160 bpm); fetal bradycardia (fetal heart rate less than 110 bpm); reduced variability (less than 5 bpm); decelerations of the fetal heart rate (early, late or variable))*; instrumental vaginal birth; emergency caesarean birth (*all and for fetal distress).*

3. **Adverse outcomes for the infant**defined as: Apgar score <7 at 5 minutes; birthweight less than 10^th ^centile for gestational age and infant sex; admission to neonatal intensive care unit (NICU) and length of stay; incidence and severity of any neonatal respiratory disease; use of and length of any mechanical ventilation; use of and length of any tube feeding.

4. **Composite of serious neonatal outcomes reflecting asphyxia**defined as one or more of: *death due to asphyxial causes*; *birth trauma *(subdural or intra-cerebral haemorrhage, spinal cord injury, basal skull fracture, other fracture, peripheral nerve injury present at discharge from hospital); *birth weight ≤ 3*^*rd *^*centile for gestational age at birth and infant sex *[8]; *Apgar score ≤ 4 at 5 minutes of age; cord pH ≤ 7.00 *[9]; *seizures at ≤ 24 hours age or requiring two or more drugs to control; neonatal encephalopathy grade 3 or 4 *[14]).

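### One pre-specified subgroup is defined by actual mode of birth, which is settled after randomisation and can be affected by the allocated policy, so effects within it can be biased

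*Protocol article*

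**What the plan says.** The subgroup list is in the Analysis and Reporting of Results section of the protocol article: "Pre-specified subgroup analyses will be by chorionicity of the pregnancy (monochorionic or dichorionic"), then "collaborating centre; and actual mode of birth". Nothing in the article restricts the last item or labels it descriptive.

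Other sections bear on that choice:

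- **Timing.** Trial Entry says that "eligible women will be randomised from 36^6 ^weeks gestation", and the Exclusion Criteria rule out women in active labour. Mode of birth is therefore always observed after allocation.
- **Baseline counterpart.** Trial Entry also says: "Stratification will be by collaborating centre and planned mode of birth (planned caesarean section or planned vaginal birth"). Planned mode is thus known for every woman before allocation, yet it is not among the named subgroups.
- **What the arms do.** For a planned vaginal birth, the Elective Birth Group section says "Where there is a plan for vaginal birth, this will involve induction of labour", while the Standard Care Group section says "this will involve either awaiting the spontaneous onset of labour, or induction of labour if required".
- **Mode of birth as an outcome.** The Background, under Benefits of induction of labour, says that the potential advantages "have to be balanced against any associated increase in the risk of caesarean section". The Secondary Study Endpoints include "instrumental vaginal birth; emergency caesarean birth".

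**The concern.** A subgroup analysis keeps the protection of randomisation only if the subgroup is defined by something that allocation cannot affect. Centre and chorionicity meet that test. Chorionicity is confirmed from the placenta after birth, but it is a fixed feature of the pregnancy. Actual mode of birth does not meet it.

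Two conditions are needed for bias, and the article makes both plausible. First, the policy can act on the route to birth: induction in one arm, awaiting labour in the other. Second, mode of birth and infant outcome share causes. Under Care of Women in Both Groups, a non-reassuring fetal heart rate trace can lead to emergency caesarean. The same fetal condition bears on the low Apgar score and low cord pH components of the primary composite.

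If unplanned caesareans arise at different rates or for different reasons in the two arms, the women within each actual-mode category are no longer comparable between arms. The subgroup could then show benefit or harm where there is none, or hide a real difference. Because it is pre-specified, readers may give it more credit than it deserves. It also mixes planned caesareans with those that follow labour, so it cannot say whether the policy works differently through induction and through elective caesarean.

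**Working it through.** The plan gives no figure for this subgroup, so there is none to reproduce. The check asks how far an actual-mode comparison can move when the policy has **no effect** on the infant outcome. All inputs below are assumptions, except where the 16.3% event rate from the Sample Size section is used for calibration.

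**Scenario A: women planning vaginal birth**

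Assumed inputs:
- 15% have hidden fetal compromise.
- Outcome risk is 50% if compromised and 10% if not, in both arms.
- Caesarean rate is 50% if compromised, in both arms.
- Caesarean rate if not compromised is 25% under elective birth and 12% under standard care.

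Overall risk in both arms: 0.15 × 0.50 + 0.85 × 0.10 = 0.160, so the true RR is 1.00.

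*Unplanned caesareans* (risk = events ÷ share of women)
- Elective: share 0.15 × 0.50 + 0.85 × 0.25 = 0.2875; events 0.075 × 0.50 + 0.2125 × 0.10 = 0.05875; risk 20.4%.
- Standard: share 0.075 + 0.85 × 0.12 = 0.177; events 0.0375 + 0.0102 = 0.0477; risk 26.9%.
- RR = 0.76.

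*Vaginal births*
- Elective: (0.160 − 0.05875) ÷ (1 − 0.2875) = 0.10125 ÷ 0.7125 = 14.2%.
- Standard: (0.160 − 0.0477) ÷ (1 − 0.177) = 0.1123 ÷ 0.823 = 13.6%.
- RR = 1.04.

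**Scenario A extended to all caesareans**

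The subgroup that the plan names would also contain women who planned a caesarean. Let q be their share, which the article does not give, and let their risk be 16% in both arms. The risk among all caesareans is then

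[0.16q + (1 − q) × events] ÷ [q + (1 − q) × share].

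| q | Elective | Standard | RR |
|---|---|---|---|
| 20% | 0.0790 ÷ 0.4300 = 18.4% | 0.0702 ÷ 0.3416 = 20.5% | 0.89 |
| 40% | 0.0993 ÷ 0.5725 = 17.3% | 0.0926 ÷ 0.5062 = 18.3% | 0.95 |
| 60% | 0.1195 ÷ 0.7150 = 16.7% | 0.1151 ÷ 0.6708 = 17.2% | 0.97 |

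Pooling planned caesareans dilutes the distortion in the caesarean category. It leaves the vaginal-birth figure unchanged.

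**Scenario B: continuous fetal frailty**

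A normally distributed frailty drives both the infant outcome (average 16.3%) and unplanned caesarean through logistic links. The log-odds slopes for outcome and caesarean are 0.8 and 1.0 (moderate) or 1.5 and 1.5 (strong). Standard care has 30% unplanned caesarean among planned vaginal births. Results are by numerical integration.

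| Assumed difference between arms | RR, vaginal births | RR, unplanned caesareans |
|---|---|---|
| Elective rate 20%, moderate / strong | 1.06 / 1.14 | 1.06 / 1.13 |
| Elective rate 30%, same indication | 1.00 | 1.00 |
| Elective rate 45%, moderate / strong | 0.92 / 0.82 | 0.92 / 0.86 |
| Both 30%, but caesarean under elective birth only weakly linked to frailty (slope 0.3), moderate / strong | 1.13 / 1.42 | 0.81 / 0.66 |

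With 40% planned caesareans added, the rate-change rows give 0.98 to 1.00 for all caesareans pooled.

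**Same check by planned mode**

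A simulation of 4,000,000 women per setting used the moderate links and no true effect. The RR by planned mode stayed at 0.99 to 1.00 in both strata, within simulation error.

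**The case against.** The strongest case on the other side has four parts.

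1. **The documents do not show that policy changes mode of birth.** A reader might infer that it does, and that these subgroup effects are therefore biased. The article does not support that. Its remark on caesarean risk is conditional, and listing emergency caesarean as an endpoint shows only that it will be measured. The one earlier randomised trial it describes found no statistically significant difference in mode of birth, although that trial had 36 women and the article itself calls it underpowered. If neither the rate nor the indication differs, every subgroup RR is 1.00. This stands: the supportable wording is *can be biased*.
2. **The RR of 0.76 does not describe the subgroup that the plan names.** It covers women planning vaginal birth only. For all caesareans the same inputs give about 0.89 to 0.97. This also stands.
3. **The main results do not depend on this subgroup.** The primary and secondary comparisons are by allocation, the sample size does not use it, and the other two subgroups are fixed before randomisation. The stated aims and hypotheses pose no question about effect by mode of birth. This stands and limits the severity.
4. **An article may leave the form of the subgroup test to a fuller analysis plan.** That is so, and the lack of a stated interaction test is not the point here. The choice of subgroup variable, however, is stated and unqualified.

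None of these makes the variable suitable. Keeping women in their allocated arm does not restore comparability once they have been selected on something that happened after allocation.

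**Conclusion.** Wrong as written; severity moderate. Treatment effects within categories of actual mode of birth are not randomised comparisons and can be biased. The documents establish neither the size nor the direction. Under the assumptions shown and with no true effect, the apparent RR runs from about 0.82 to 1.42 in vaginal births and from about 0.66 to 1.13 in unplanned caesareans. For all caesareans pooled it is nearer 1, at about 0.89 to 0.97 in Scenario A and 0.98 to 1.00 in the Scenario B settings where only the rate changes. It is 1.00 throughout if the policy alters neither the rate of caesarean nor its indication.

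A reader should not infer that the trial's main conclusion is at risk: the intention-to-treat analyses and the subgroups by chorionicity and centre are unaffected.

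**What to change.** In the subgroup list, replace actual mode of birth with planned mode of birth as recorded at randomisation. Assess it with a treatment-by-planned-mode interaction term in the planned model for the outcome. Report actual mode of birth by arm as an outcome or descriptively, with no treatment-effect estimates within its categories.

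The cost is a wording change. Planned mode is already collected before allocation and used for stratification, so no extra women, visits or data are needed and nobody's care changes. The change should be made before outcome data are examined by arm, and so ideally before the interim analysis planned at 230 women.
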